### Data collection and storage

The registry will exploit data available from:

national or regional registries/databases (DBs) dedicated to rare head and neck cancers (i.e. nasopharynx; nasal cavity and paranasal sinuses; salivary gland; and middle ear cancers)HCP registries/DBs;ad hoc data collection by HCPs.

The registry is federated thus, data are stored by the data provider (i.e. national/regional registries and/or HCP). At the local level, data are pseudonymised.

### Data analyses

The Personal Health Train (PHT) enables data from multiple organizations to be analysed without identifiable data leaving the organization. By keeping data at its source, no copies of datasets are generated and/or shared with third parties. Vantage6 is the open source implementation of the PHT (https://www.vantage6.ai). Vantage6 uses the mathematical principle of “federated learning”, typically applied to horizontally partitioned data (i.e. organizations have data from different patient cohorts, but with similar characteristics/items). Federated learning is based on the mathematical principle of splitting computations into (a) parts at the station (local HCP or registry) and (b) a central part. The stations share sub-computations with the central server only. If federated learning does not work, the data, after quality validation, will be anonymised and sent to the coordination centre (i.e. National Cancer Institute of Milan [Fondazione IRCCS Istituto Nazionale dei Tumori, Milan-INT]).

Statistical analyses will be performed based on a study protocol (please refer to the Governance section). Queries will be developed, in collaboration with clinical experts, to interrogate the EURACAN rare head and neck cancers registry to generate the descriptive statistics and relevant information needed to plan the analyses envisaged by the study protocol. Queries may include general description of the characteristics of the patients or of the cancer included in the registry such as: gender, mean age, cancer site, cancer histology, stage, treatment at diagnosis etc. Due to the nature of the registry, supplementary statistical analysis plans are envisioned to reply to specific research questions arising over time. Secondary analyses, developed after making observations, expected or unexpected, on the registry will be identified and highlighted as hypothesis generating. Positive finding could be used for developing a rationale for further studies or grants. Several analyses will be performed, but here we report a general data analysis plan based on the four objectives of the registry.

### Data analyses plan

The data analyses will include descriptive statistics showing frequency and patterns of patients’ and cancers’ variables; analytical analyses investigating the association of patients/disease and/or treatment characteristics and health outcomes.

Descriptive statistics will be used to reconstruct the natural history of rare head and neck cancers (e.g. primary tumour growth rate and pattern, its metastatic dissemination, growth of metastases, association with other diseases etc.) and to report indicators about quality of care.

Multivariable Cox’s proportional hazards model and Hazard ratios (HR) for all-cause or cause specific mortality will be used to determine independent predictors of overall survival, recurrence and second primary cancer. Variables to include in the multivariable regression model will be selected based on the results of univariable analysis or using Information Criteria, such as Akaike Information Criterion. According to the specific research question the role of potential confounders and effect modifiers will be evaluated. Confounders will be included in the model and sensitivity analysis will be performed. Stratified analyses will be performed in the presence of effect modifiers that will be detected by testing the interaction between the predictors and the variable.

To assess treatment effectiveness multivariable models with propensity score adjustment that can remove bias due to real world nature of the registry and progression-free survival will be performed.

High proportion of missing data threaten the validity of the inferences/prognostic models. Thus, a maximum of 10% of missing data will be allowed and missing data will be imputed using strategy such as unconditional/conditional mean or expectation maximum.

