**Objectives:**

**Methods:**

Settings and participants

It is an hospital based registry established in hospitals with expertise in head and neck cancers. Only adult patients with epithelial tumours of nasopharynx; nasal cavity and paranasal sinuses; salivary gland cancer in large and small salivary glands; and middle ear will be included in the registry. This registry won’t select a sample of patients. Each patient in the facility who meets the above mentioned inclusion criteria will be followed prospectively and longitudinally with follow-up at cancer progression and / or cancer relapse or patient death. It is a secondary use of data which will be collected from the clinical records. The data collected for the registry will not entail further examinations or admissions to the facility and/or additional appointments to those normally provided for the patient follow-up.

Variables

Data will be collected on patient characteristics (eg. patient demographics, lifestyle, medical history, health status); exposure data (eg. disease, procedures, treatments of interest) and outcomes (e.g. survival, progression, progression-free survival, etc.). In addition, data on potential confounders (e.g. comorbidity; functional status etc.) will be also collected.

Statistical methods

The data analyses will include descriptive statistics showing patterns of patients’ and cancers’ variables and indicators describing the quality of care. Multivariable Cox’s proportional hazards model and Hazard ratios (HR) for all-cause or cause specific mortality will be used to determine independent predictors of overall survival, recurrence etc. Variables to include in the multivariable regression model will be selected based on the results of univariable analysis. The role of confounding or effect modifiers will be evaluated using stratified analysis or sensitivity analysis. To assess treatment effectiveness, multivariable models with propensity score adjustment and progression-free survival will be performed. Adequate statistical (eg. marginal structural model) methods will be used if time-varying treatments/confounders and confounding by indication (selective prescribing) will be present.

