The registry initiated on the rare head and neck cancers including nasal cavity and paranasal sinuses (incidence rate 0.5/100,000), nasopharynx (incidence rate 0.5/100,000), salivary gland (incidence rate 1.5/100,000) and middle ear cancers (incidence rate 0.03/100,000), corresponding to 2,500, 2,500, about 8,000 and about 200 new cases/year in Europe, respectively (http://rarecarenet.istitutotumori.mi.it/analysis.php). Cancer care for head and neck cancers is complex in particular for the rare ones. Knowledge is limited, diseases often need multidisciplinary approach, including surgery, radiation, and systemic treatments. Patients tend to be older, to have comorbidities and less social support [5]. Moreover, while most head and neck cancers are predominantly squamous cell carcinomas, salivary gland tumours include more than 20 distinct histological subtypes. A similar consideration holds for paranasal sinus cancers. Thus, heterogeneity adds complexity to the rarity.

Our hypothesis is that the registry, gathering data on rare head and neck cancers, will support research to increase their understanding. The new evidence will contribute to develop and/or ameliorate clinical practice guidelines, to support multidisciplinary discussion and consultations for patients with rare head and neck cancers and ultimately to improve quality of care across Europe.

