## Materials and methods

Registry aims

to help describe the natural history of rare head and neck cancers;to evaluate factors that influence prognosis;to assess treatment effectiveness;to measure indicators of quality of care.

Furthermore, the registry aims to collect information, where available, on the storage of biological samples at the premises of the participating healthcare providers (HCPs). This will facilitate future studies on rare head and neck cancers biology.

Design and setting

The registry is designed to prospectively collect clinical data derived from diagnostic tests and treatments performed by the HCP as part of patient management. The data collected for the registry will not entail further examinations or admissions to the HCP and/or additional appointments to those normally provided. In other words, it will be an observational, registry-based cohort study including only people with rare head and neck cancers.

The EURACAN Registry will include EURACAN HCPs (across 7 different EU member States) and will be open to other expert HCPs, not yet in EURACAN but with proven experience in rare head and neck cancers.

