### Sample size

This is an observational clinical registry which implies a long-term data collection lasting until all the registry objectives are met. Only HCPs that treat at least 100 cases a year of all rare head and neck cancers are EURACAN member. As of April 2022, the registry is activating 10 HCPs and, with time, is envisioning to at least duplicate the number of data providers. Considering that we expected 6 centres in Italy, 2 centres in Germany, 1 centre in Czech Republic, 1 centre in Spain, 2 centres in France (400 cases per year)and the whole rare head and neck cases in The Netherlands (300 patients yearly, based on incidence estimations), we expect about 1700 patients with a rare head and neck cancer yearly.

Due to the observational nature of the registry, sample size justification is based on the precision of the estimates presented in terms of width of two-sided 95% Confidence Interval (CI) for a single proportion using the Simple Asymptotic method (in case of categorical variables) and in form of normal distribution for means (in case of continuous variables). Thus, for example, for a categorical endpoint (e.g., proportion) a sample size of 80 patients (e.g. middle ear cases in 4 years) will achieve a maximum width of 95% CI on estimated proportions of 23.4% (i.e. estimated proportion +/- 11.7%). For continuous endpoints, a sample size of 80 patients will achieve a maximum width of 95% CI on estimated means of 0.46*SD (i.e. estimated mean +/- 0.23*SD, where SD = Standard Deviation).

Table 1 reports the precision of the estimates for categorical and continuous endpoint under different sample size.

**Table 1 pone.0283071.t001:** Precision of the estimates expressed as 95% Confidence Interval (CI) for categorical and continuous endpoint accordingly to different sample size.

		
	Categorical endpoint		Continuous endpoint	
Target sample size	max 95% CI	Width of 95% CI (%)	max 95% CI	Width of 95% CI
1000	Estimate +/-0.03	0.06	Estimate +/- 0.06*SD	0.12*SD
250	Estimate +/- 0.06	0.12	Estimate +/- 0.12*SD	0.24*SD
80	Estimate +/- 0.11	0.22	Estimate +/- 0.22*SD	0.44*SD
70	Estimate +/- 0.12	0.24	Estimate +/- 0.23*SD	0.46*SD
60	Estimate +/- 0.13	0.26	Estimate +/- 0.25*SD	0.50*SD
50	Estimate +/- 0.14	0.28	Estimate +/- 0.27*SD	0.55*SD

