For the analytical questions involving several different outputs and variables, it is not possible to define a summary of the sample size calculation. For this reason ad hoc analysis plans for each research question are envisioned.

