### Outcomes

Primary outcomes with a time frame of 1 year include:

Overall survival (all cause and/or cause specific)Disease free survivalTreatment response: the percentage of patients whose cancer shrinks or disappears after treatment. Treatment response expressed as a complete response; partial response; stable disease; progression based on clinical judgment on imaging.Cancer treatment observed adverse events: incidence of cancer treatment adverse events as assessed by Common Terminology Criteria for Adverse Events (CTCAE)Surgical complications: percentage of patients with surgical complications as assessed by the Clavien-Dindo ClassificationQuality of care: percentage of patients treated according to clinical practice guidelines for head and neck cancer.

Predictors of mortality and/or tumor response include but are not limited to:

Patients’ Characteristics (age, gender, educational level, tobacco, comorbidity, virus status when appropriate)Tumor Characteristics (site, histology, T,N,M, clinical and pathological stage, tumour mutation)Treatment Characteristics (radiotherapy alone, surgery alone, systemic therapy alone, multimodal therapy)

Exposures will mainly include different type of treatment (radiotherapy alone, surgery alone, systemic therapy alone, multimodal therapy)

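### The analysis plan takes predictors of recurrence and second primary cancer from mortality hazard ratios, whose event is death and not the endpoint named

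*Protocol article*

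**What the plan says.** The section "Data analyses plan" names a multivariable Cox model and one effect measure for the prognostic analyses: "Hazard ratios (HR) for all-cause or cause specific mortality will be used to determine independent predictors of overall survival, recurrence and second primary cancer". The abstract, under statistical methods, has nearly the same sentence: "Hazard ratios (HR) for all-cause or cause specific mortality will be used to determine independent predictors of overall survival, recurrence etc". This analysis serves the registry aim "to evaluate factors that influence prognosis".

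Under "Outcomes", the first primary outcome is "Overall survival (all cause and/or cause specific", followed by a closing bracket. Disease-free survival is listed separately. Neither recurrence alone nor second primary cancer is a listed outcome, and nowhere is time to either one named as the modelled event.

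The article leaves detail to later documents. Under "Sample size" it says that "ad hoc analysis plans for each research question are envisioned", and under "Data analyses" it says "here we report a general data analysis plan based on the four objectives of the registry".

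**The concern.** A hazard ratio belongs to the event that is counted. If the event is death, the ratio describes the rate of dying. Recurrence and second primary cancer each need their own event and event time.

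The gap matters in this population. The Introduction says of these patients: "Patients tend to be older, to have comorbidities and less social support". Deaths without recurrence are therefore to be expected, and age and comorbidity are among the predictors listed under "Outcomes". Followed literally, the rule would credit such factors with driving recurrence because they drive death. It would also understate factors that raise recurrence but act on survival only through it. Cancer-specific mortality is not a clean substitute, because it mixes the risk of recurring with survival after recurrence.

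**Working it through.** **No stated figure to reproduce.** The article gives no target hazard ratio, event rate or number of events for these endpoints. Its "sample size justification is based on the precision of the estimates presented in terms of width of two-sided 95% Confidence Interval (CI"), for one proportion or one mean. The size below therefore rests on assumed rates.

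**Assumptions (none from the documents).** Exponential times; a binary factor carried by half the patients; recurrence at λ = 0.10 per year; death without recurrence at δ = 0.06 per year (range 0.03 to 0.10); death after recurrence at μ = 0.5 per year, counted as cancer death; follow-up cut at 5 years; 40,000 simulated patients per scenario. A Cox model was fitted to each event.

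| Assumed effect of the factor | HR, recurrence (cause-specific) | HR, all-cause death | HR, cancer death |
|---|---|---|---|
| None on recurrence; other-cause death × 2.5; δ = 0.03 | 1.00 | 1.48 | 1.04 |
| Same, δ = 0.06 | 0.97 | 1.74 | 1.05 |
| Same, δ = 0.10 | 0.98 | 1.93 | 1.17 |
| Doubles recurrence only | 1.99 | 1.43 | 1.90 |
| Doubles death after recurrence only | 1.02 | 1.22 | 1.34 |

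The recurrence model recovers the true values (1, 1, 1, 2 and 1) within simulation error. The mortality models do not.

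**Closed-form check of the second row.** The share alive without recurrence at time t is S = exp(−(λ+δ)t). The share alive after recurrence is P = λ/(μ−λ−δ) × [exp(−(λ+δ)t) − exp(−μt)]. The all-cause hazard among those alive is (δS + μP)/(S + P).

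- At t = 0 everyone is recurrence-free, so the ratio is 0.15/0.06 = 2.5.
- At 1 year, without the factor: S = 0.8521, P = 0.0722, hazard 0.0944. With it (δ = 0.15): S = 0.7788, P = 0.0689, hazard 0.1785. Ratio 0.1785/0.0944 = 1.89.
- At 5 years, without the factor: S = 0.4493, P = 0.1080, hazard 0.1453. With it: S = 0.2865, P = 0.0818, hazard 0.2277. Ratio 0.2277/0.1453 = 1.57.

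The fitted 1.74 is a weighted average over this path, and the recurrence hazard ratio is 1 throughout. The mismatch is larger at short horizons, so the 1-year time frame given under "Outcomes" does not remove it.

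**Why cancer death also misleads.** Its hazard among those alive is μP/(S + P), which depends both on how many have recurred and on how fast they then die. A factor that changes only μ therefore moves it, as the last row shows.

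**The case against.** The strongest reply is that the sentence can be read more kindly: Cox models for each endpoint, with the mortality hazard ratio attached only to survival. Disease-free survival is a separate outcome and progression-free survival is named elsewhere, so recurrence-type events are collected and analysed. The authors may well have meant this. But the text does not say so, the abstract repeats the pairing, and no section names recurrence or second primary cancer as a modelled event.

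A second reply is that this is a general plan and question-specific plans will follow. That excuses missing detail. It does not excuse a wrong event, which later plans would inherit. It does cover the choice of competing-risk estimator: a Cox model for recurrence censored at death is valid for identifying predictors, and the lack of cumulative-incidence detail here is not an error.

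A third reply is that the plan also allows cause-specific mortality, which nearly removes the bias for a factor acting only on other-cause death (1.04 to 1.17 in the table). That is correct for that kind of factor. It fails for one acting after recurrence (1.34).

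A reader might go further and infer that risks of recurrence will be estimated as one minus Kaplan-Meier, so that the natural-history figures will come out too high. The article does not support this. It names no estimator of recurrence risk and says only that natural history will be described with descriptive statistics.

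**Conclusion.** The point holds as a misstatement of the event in the general plan. A mortality hazard ratio is not a measure of effect on recurrence or second primary cancer, and the sentence, taken as written, would yield wrong predictors for both.

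That conclusion needs no assumption about rates; only its size does. Under the assumed rates over 5 years, a null factor for recurrence can appear with an all-cause mortality HR of about 1.5 to 1.9, a doubling of recurrence can shrink to about 1.4, and a factor with no effect on recurrence can show about 1.3 on cancer-specific mortality. Other rates would give other values.

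A lesser, linked point is the outcome label. Overall survival is all-cause by definition, so the and/or wording leaves the event of a primary outcome open.

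**What to change.** Reword the sentence in "Data analyses plan", and its counterpart in the abstract, so that each endpoint has its own event and its own Cox model:

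- overall survival: death from any cause;
- cause-specific survival: death from the cancer, listed under "Outcomes" as an outcome separate from overall survival;
- recurrence: first recurrence, as a cause-specific hazard censored at death;
- second primary cancer: its diagnosis, as a cause-specific hazard censored at death.

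Add one sentence: where absolute risks of recurrence or second primary cancer are reported, they are estimated as cumulative incidence with death as a competing event. Further detail can stay with the question-specific plans.

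The cost is wording only. The abstract already provides for follow-up at progression, relapse or death, and cause of death is needed for the cause-specific outcome already listed. The one item to confirm is that the code book records the date of a second primary cancer.

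### Predictors of recurrence and second primary cancer are assigned mortality hazard ratios, which are the wrong effect measure for these non-fatal events

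*Protocol article*

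**What the plan says.** The protocol article, under Data analyses plan, names a multivariable Cox model and then states: "Hazard ratios (HR) for all-cause or cause specific mortality will be used to determine independent predictors of overall survival, recurrence and second primary cancer". The abstract, under Statistical methods, has the same construction: "Hazard ratios (HR) for all-cause or cause specific mortality will be used to determine independent predictors of overall survival, recurrence etc". It does not name second primary cancer.

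The section Data analyses introduces this text with the words "here we report a general data analysis plan based on the four objectives of the registry". Under Sample size, the article adds: "For this reason ad hoc analysis plans for each research question are envisioned".

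The Outcomes section lists overall survival (all-cause and/or cause-specific) and disease free survival. It lists neither time to recurrence nor time to second primary cancer. Its list of predictors, which includes age and comorbidity, is for mortality and tumour response. Progression-free survival is tied to the treatment-effectiveness aim. The Introduction says of the patients: "Patients tend to be older, to have comorbidities and less social support".

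**The concern.** Recurrence and second primary cancer are events with their own times and their own hazards. A hazard ratio for death combines up to three things: the rate of relapse, survival after relapse and, for all-cause mortality, death from other causes. A covariate can act on the last two without touching the first. In the article, cause-specific qualifies mortality only, so it does not supply a cause-specific hazard of recurrence.

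Evaluating factors that influence prognosis is one of the four registry aims. Age and comorbidity, which plausibly raise other-cause death, are among the candidate predictors. If the sentence is applied as it stands, such factors could be called independent predictors of relapse or of a new cancer when they are not.

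**Working it through.** The plan states no figure for this analysis, so there is none to reproduce. The check has two parts.

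**1. The text.** Two places, the abstract and the analysis plan, attach mortality hazard ratios to recurrence. No other section defines a hazard or an outcome for recurrence or second primary cancer. Disease free survival is listed, but it is not linked to these predictors, and it counts deaths as events.

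**2. The size, under assumed rates.** All rates here are assumptions.

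*Case A: a factor that acts only on other-cause death.* Recurrence hazard is 0.10 per year in both groups, so the true recurrence hazard ratio is 1.0. Cancer death after relapse is 0.40 per year in both groups. Other-cause death is 0.02 per year without the factor and 0.06 to 0.12 with it.

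Among those alive at time t, the share who have relapsed is p(t) = R/(R + N), with
- N = exp(−0.10t)
- R = [0.10/(0.40 − 0.10)] × [exp(−0.10t) − exp(−0.40t)]

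The all-cause death hazard is the other-cause rate plus 0.40 × p(t). Other-cause death is assumed to be the same before and after relapse, so p(t) is equal in the two groups.

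| t (years) | p(t) | 0.40 × p(t) | Ratio, 0.06 v 0.02 | Ratio, 0.12 v 0.02 |
|---|---|---|---|---|
| 0 | 0 | 0 | 0.06/0.02 = 3.0 | 0.12/0.02 = 6.0 |
| 1 | 0.0782/0.9830 = 0.080 | 0.0318 | 0.0918/0.0518 = 1.77 | 0.1518/0.0518 = 2.93 |
| 2.5 | 0.1370/0.9158 = 0.150 | 0.0598 | 0.1198/0.0798 = 1.50 | 0.1798/0.0798 = 2.25 |
| 5 | 0.1571/0.7636 = 0.206 | 0.0823 | 0.1423/0.1023 = 1.39 | 0.2023/0.1023 = 1.98 |

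The ratio changes over time, so a single Cox estimate is an average. Over 5 years, simulation gives about 1.5 to 1.6 at the low end and 2.4 at the high end. With recurrence as the event and death censored, the hazard ratio is 0.97 to 1.01. With cancer-specific mortality it is also about 1, so this factor misleads only under the all-cause option.

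*Case B: a factor that acts only after relapse.* Recurrence hazard is again 0.10 per year in both groups. Post-relapse cancer death is 0.80 v 0.30 per year. At 2.5 years:
- Rate 0.30: R = (0.10/0.20) × (0.7788 − 0.4724) = 0.1532; p = 0.1532/0.9320 = 0.1644; cancer-death hazard 0.30 × 0.1644 = 0.0493.
- Rate 0.80: R = (0.10/0.70) × (0.7788 − 0.1353) = 0.0919; p = 0.0919/0.8707 = 0.1056; cancer-death hazard 0.80 × 0.1056 = 0.0845.
- Cancer-mortality ratio: 0.0845/0.0493 = 1.71. The simulated 5-year Cox estimate is 1.7.
- All-cause ratio, adding 0.02 other-cause death to each: 0.1045/0.0693 = 1.51.
- The recurrence hazard ratio is about 1.

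This factor misleads under either mortality option.

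**Wider check.** A second set of simulations (40,000 patients each, 5 years) used event hazards of 0.02 to 0.10 per year and a factor that multiplies the death hazard by 2 or 3 with no effect on the event. Mortality hazard ratios were 1.81 to 2.02 and 3.03 to 3.08 respectively, which mainly reflect the assumed multiplier. The event's own cause-specific hazard ratio was 0.97 to 1.08. The composite of event or death gave 1.33 to 2.79, so disease free survival would not repair the problem.

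**The case against.** The best defence is grammatical. The sentence names the Cox model first and the mortality hazard ratios second, and it has three endpoints. It can be read as one Cox model per endpoint, with mortality hazard ratios meant for survival. On that reading a factor acting only on death would show a hazard ratio of about 1 for recurrence, and the fault shrinks to loose wording. This is a fair reading and it lowers the severity. It does not remove the point, because the article never says that each event has its own model.

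It is also true that this is a general plan, with question-specific plans and Steering Committee review of study protocols to follow. These could correct the endpoint. A reader might infer that false predictors will be reported; the documents support only that they would be if the sentence were followed.

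Three further inferences go too far:
- That the missing competing-risk method is a separate fault. A condensed article commonly leaves that choice to the analysis plan.
- That absolute risks will be overstated by using one minus Kaplan-Meier. The article nowhere proposes this.
- That age and comorbidity would be mislabelled through other-cause death whichever mortality measure is chosen. That needs the all-cause option.

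Finally, the only time frame given for outcomes is 1 year, whereas the calculations run to 5. In case A the mortality ratio is larger early on (1.77 to 2.93 at 1 year), so a shorter frame does not make the mislabelling smaller, although there would be fewer deaths to estimate it from.

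**Conclusion.** The point holds as a moderate correction. The analysis plan and the abstract pair mortality hazard ratios with recurrence, and the analysis plan also with second primary cancer. This is a mismatch in what the article states, not a detail left for later. Applied literally, a factor with no effect on the event could carry a mortality hazard ratio of roughly 1.5 to 2.4 and be labelled a predictor of it. That range rests wholly on assumed rates, because the documents give none; the direction of the error does not depend on them. Whether it would reach a report depends on how the authors meant the sentence and on what the later plans specify.

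**What to change.** Reword the sentence under Data analyses plan and its counterpart in the abstract along these lines:
- Recurrence and second primary cancer are each the event in their own cause-specific Cox model. Death without the event is a competing event, censored when the cause-specific hazard is estimated.
- Hazard ratios for all-cause or cause-specific mortality are used for mortality only.
- If absolute risks of recurrence or second primary cancer are reported, they are cumulative incidences that allow for death.

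A Fine-Gray model should not replace the cause-specific model for identifying predictors. In the wider check it gave 0.55 to 0.88 for a factor with no effect on the event hazard, because earlier deaths leave fewer patients to have the event.

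The cost is a change of wording in two places and a little more analysis. It needs no additional patients. The models need the dates of recurrence, second primary cancer and death; the article already plans to collect progression and death as outcomes.
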